#### Health-related quality of life (HRQOL) and parental distress and anxiety

HRQOL of the operated infants, parental distress and parental anxiety will be measured by three different validated questionnaires next to the socio-demographic list. HRQOL of the operated infants will be calculated using the TAPQOL (TNO-AZL Preschool Children Quality of Life) [26] scores, with higher scores (range 0–100) indicating better HRQOL. Parental distress and anxiety levels will be calculated using the State-Trait Anxiety Inventory (STAI) [27] and the Distress Thermometer for Parents (DT-P) [28], indicating greater distress and anxiety when revealing higher scores. The questionnaires will be completed by the parents/caretakers at baseline before surgery, 4 weeks and 1 year after primary hernia repair and, if relevant, prior to and 4 weeks after re-operation for MCIH.

## Participant timeline {13}

### Baseline assessment

After enrolment of participants in the study, demographics and baseline characteristics including sex, date of birth, medical history, gestational age, birth weight, side of the inguinal hernia and other hernia characteristics (e.g. history of incarceration) will be collected. Also, parents/caretakers receive four questionnaires (TAPQOL, State STAI, the DT-P and EQ-5D-5L (EuroQol 5D) that we ask them to complete before the intervention (Fig. 1).

**Fig. 1 Fig1:**
[figure not shown]
Flow chart of participants included in the study

### Post intervention assessment

Primary and secondary outcomes will be assessed during hospital admission, 4 weeks after primary hernia repair and 1 year after primary hernia repair. If patients develop MCIH within 1 year after primary inguinal hernia repair, baseline and outcome assessments will also be performed during and 4 weeks after MCIH repair.

## Sample size {14}

Data from the latest systematic review shows that the incidence of infants younger than 6 months of age who develop MCIH is 12.4% [4]. Retrospective data from the Emma Children’s Hospital AMC, where in 2000/2001 contralateral exploration was routinely performed, shows similar results: 8/92 patients did not undergo contralateral exploration and subsequently one patient (12.5%) developed MCIH. Eighty-four patients underwent unilateral hernia repair with contralateral exploration of which one patient (1.2%) developed MCIH.

The expected percentage of children requiring one or more reoperations because of MCIH in the first year following hernia repair is approximately 10%. We consider a reduction of children requiring reoperation from 10 to 2.5% as clinically relevant. A total sample size of 378 patients is needed to detect such a reduction with a power of 0.80 at a two-sided alpha of 0.05 (nQuery Advisor 7.0) [29]. Taking into account 10% loss to follow-up, we need to include 416 children.

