Surgeons may prefer performing contralateral exploration because of high MCIH incidence, high incarceration rate and repeated anaesthesia, carrying risk for near critical incidents (apnoea risk up to 12%) [12]. The US Food and Drug Administration (FDA) recently released an official warning regarding the potentially harmful impact of repeated general anaesthesia on the child’s brain [13]. Indeed, previous studies have shown that multiple exposures to general anaesthesia before 3 years of age is associated with neurocognitive and developmental problems (e.g. learning disabilities) [14–17]. More recent research has shown that the potential impact of a single session of general anaesthesia for hernia repair on functional brain development is not detectable [18, 19]. Yet, the effect of repeated anaesthesia on brain development remains unclear [13, 18]. These findings highlight the importance of preventing repeated surgery and anaesthesia. Contralateral exploration may help to reduce the frequency and total length of anaesthesia in children that develop MCIH after unilateral hernia repair.

Nonetheless, contralateral exploration also carries additional risks of operative complications: wound infection occurs in 0.6–1.2% of the children, hematoma in 0.1%, testicular atrophy in 0–0.3% and ipsilateral recurrence in 0.4–1.2% [20, 21]. In preterm babies, these risks are even higher: the recurrence rate varies from 2 to 8.6% and the risk of testicular atrophy, which may be accompanied by loss of function, ranges from 2 to 30% [3, 5]. If both testes are affected, boys may become infertile. As not all PPVs necessarily become hernias, contralateral exploration and its additional risks will be unnecessary in some children [22]. Consequently, the debate continues whether or not to perform contralateral inguinal exploration in infants with inguinal hernia [4, 9, 20]. Cost-effectiveness of both strategies in children has never been assessed.

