## Outcomes {12}

### Primary outcome measure

Primary outcome is the proportion of reoperations within 1 year after primary hernia repair. This will be calculated using the number of infants that undergo a second operation related to inguinal hernia repair within 1 year following primary repair, as a fraction of the total number of infants in that group. All participants are seen by a (fellow) paediatric surgeon at the outpatient clinic or via a digital consult 1 year after primary hernia repair. The latter is done to score development of contralateral hernia, testicular atrophy and/or recurrence.

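### The stated power of 0.80 rests on a control rate for MCIH reoperation alone, while the primary endpoint also counts reoperation for recurrence

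*Protocol article*

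**What the plan says.** **Basis of the sample size** (Protocol article, Sample size {14}). The control-arm input is tied to one cause: "The expected percentage of children requiring one or more reoperations because of MCIH in the first year following hernia repair is approximately 10" per cent. The evidence behind it is also about MCIH. The systematic review is cited for the statement that "the incidence of infants younger than 6 months of age who develop MCIH is 12.4" per cent, and the single-centre series for the statement that "Eighty-four patients underwent unilateral hernia repair with contralateral exploration of which one patient (1.2%) developed MCIH". The target follows without naming a cause: "We consider a reduction of children requiring reoperation from 10 to 2.5% as clinically relevant". The result is: "A total sample size of 378 patients is needed to detect such a reduction with a power of 0.80 at a two-sided alpha of 0.05".

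**Endpoint to be tested** (Primary outcome measure). The numerator is "the number of infants that undergo a second operation related to inguinal hernia repair within 1 year following primary repair". Neither this section, the abstract nor the Primary study parameter section limits it to MCIH. The section on complications defines recurrence as a hernia on the side already operated on that warrants another operation there. A reoperated recurrence within the year is therefore a primary event.

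**Recurrence rates** (Background and rationale {6a}). Ipsilateral recurrence is put at 0.4–1.2% in children generally. For preterm babies, "the recurrence rate varies from 2 to 8.6" per cent. Preterm infants can enter the trial: no exclusion concerns gestational age, recruitment includes the NICU, and gestational age below 37 weeks is a planned subgroup.

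**The concern.** The power statement and the endpoint count different events. Exploring the other groin cannot prevent recurrence in the groin with the original hernia. Such reoperations fall in both arms and raise both event rates without widening the difference. Variance rises and the odds ratio, which is the planned effect estimate, shrinks towards 1. A non-significant or borderline result would then be read against a power of 0.80 that was not worked out for this endpoint. A real reduction in MCIH reoperation could also be partly hidden by recurrences.

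**Working it through.** **Inputs.** Two-sided alpha 0.05, power 0.80, 10% v 2.5% (Sample size {14}); 1:1 allocation (Sequence generation {16a}); recurrence 0.4–1.2% in general and 2–8.6% in preterm babies (Background and rationale {6a}); MCIH after exploration 1/84 = 1.2% (Sample size {14}).

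**Step 1: reproduce 378.** With p1 = 0.10, p2 = 0.025, mean p̄ = 0.0625 and d = 0.075:

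- n0 = [1.960·√(2p̄(1−p̄)) + 0.8416·√(p1(1−p1)+p2(1−p2))]² / d² = [1.960·0.3423 + 0.8416·0.3382]² / 0.005625 = 162.3 per arm.
- With continuity correction, n = (n0/4)·[1 + √(1 + 4/(n0·d))]² = 188.06, so 189 per arm and 378 in total. This matches exactly.
- Without correction it would be 163 per arm, 326 in total.

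The arithmetic is therefore right for 10% v 2.5%, using the corrected formula.

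**Step 2: add recurrence.** Assume that r is added equally to both arms and that the MCIH effect stays at 10% v 2.5%. Then p1 = 0.10 + r, p2 = 0.025 + r, and d remains 0.075. Inverting the corrected formula at 189 per arm gives an effective size n* = (189 − 1/d)²/189 = (189 − 13.33)²/189 = 163.3, and

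power = Φ{[d·√n* − 1.960·√(2p̄(1−p̄))] / √(p1(1−p1)+p2(1−p2))}.

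For r = 1.2%: (0.9583 − 1.960·0.3714)/0.3675 = 0.627, so power is 0.73. Uncorrected power uses 189 in place of n*.

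| r | Rates | Power, corrected | Power, uncorrected | Total N for 0.80, corrected |
|---|---|---|---|---|
| 0 | 10.0% v 2.5% | 0.80 | 0.86 | 378 |
| 0.4% | 10.4% v 2.9% | 0.78 | 0.84 | 396 |
| 1.2% | 11.2% v 3.7% | 0.73 | 0.80 | 436 |
| 2% | 12.0% v 4.5% | 0.69 | 0.76 | 472 |
| 8.6% | 18.6% v 11.1% | 0.48 | 0.54 | 756 |

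The last row is an outer bound only: it treats every infant as preterm at the top of the range. Exact Fisher power at 189 per arm shows the same pattern: 0.835, 0.807, 0.756 and 0.710 for the first four rows. The crude odds ratio falls from 4.33 (r = 0) to 3.28 (r = 1.2%) and 2.89 (r = 2%).

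**Step 3: the favourable reading.** Suppose the 2.5% already covers all causes and exploration lowers MCIH to 1.2%. With r = 1.2% in both arms the rates are 11.2% v 2.4%, so d = 0.088 and n* = (189 − 11.36)²/189 = 167.0. Power is 0.89 corrected and 0.93 uncorrected.

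**The case against.** The case against has four parts.

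- **The target names no cause.** Only the 10% is labelled MCIH. The 2.5% is a clinically relevant target, and it lies 1.3 points above the 1.2% MCIH rate reported with exploration, which is enough room for the general recurrence rate. This stands, and Step 3 shows the consequence. It does not remove the problem. If 10% is also all-cause, it equals the rate that the preceding sentence gives for MCIH alone, which leaves nothing for recurrence in the control arm. The 1.2% is also a single event in 84.
- **The loss is small.** The planned analysis is logistic regression, not a continuity-corrected test, so the uncorrected figures are arguably closer to it. At the general recurrence rates they stay at 0.80–0.84. This stands.
- **A rate of 2% for everyone is not an estimate.** It is the lower end of the preterm range applied to the whole sample, and no preterm share is given. This stands, so no single replacement power should be written in.
- **Causes can already be separated.** Recurrence is a defined complication with its own analysis, and contralateral hernia and recurrence are both scored at one year. This also stands. Making MCIH reoperation a named key secondary endpoint would be a preference, not a correction.

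A reader might go further and infer that exploration roughly doubles recurrence because a second groin is opened. The documents give no such rate. The contralateral side is repaired only if a hernia or PPV is found, so an explored but unrepaired groin cannot have a recurrence of a repair.

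**Conclusion.** The mismatch is real: a control rate for one cause of reoperation supports the power of an endpoint that counts others as well. The figure of 0.80 holds for 10% v 2.5% with no recurrence added. With r between 0.4% and 2% in both arms and the MCIH effect held at 10% v 2.5%, power at 189 per arm is about 0.69–0.78 by the protocol's own method and 0.76–0.84 uncorrected. The loss is modest at the general recurrence rates. It becomes larger as preterm infants contribute more, and that share is not in the document.

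A reader might infer that the trial is underpowered or that 378 was miscalculated. The documents support neither. The total reproduces exactly, and a larger true effect on MCIH would bring power to about 0.89–0.93 even with r = 1.2%. Type I error, the endpoint and the effect estimate are unaffected. This is a power statement to correct, not a fault that threatens the trial's validity.

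**What to change.** Leave the enrolment target as it is. In Sample size {14}:

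1. Say whether 10% and 2.5% are MCIH-only or all-cause rates.
2. State the expected all-cause hernia-related reoperation rate in each arm, with the recurrence allowance and the assumed preterm share behind it.
3. Restate power for that endpoint as a range: about 0.69–0.78 corrected and 0.76–0.84 uncorrected for r = 0.4–2%, extended if the assumed preterm share implies a higher r. Note that 0.80 applies only to 10% v 2.5% with no recurrence added.
4. Report primary-endpoint events in each arm split by cause (MCIH or recurrence), using data already being collected.

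The cost is a few sentences and one descriptive table, with no extra patients or data collection. The downside is that the stated power becomes slightly less favourable.

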**Methods:**

The Hernia-Exploration-oR-Not-In-Infants-Analysis (HERNIIA) study is a multicentre randomised controlled trial with an economic evaluation alongside to study the (cost-)effectiveness of contralateral exploration during unilateral hernia repair. Infants aged 6 months or younger who need to undergo primary unilateral hernia repair will be randomised to contralateral exploration or no contralateral exploration (*n* = 378 patients). Primary endpoint is the proportion of infants that need to undergo a second operation related to inguinal hernia within 1 year after primary repair. Secondary endpoints include (a) total duration of operation(s) (including anaesthesia time) and hospital admission(s); (b) complications of anaesthesia and surgery; and (c) participants’ health-related quality of life and distress and anxiety of their families, all assessed within 1 year after primary hernia repair. Statistical testing will be performed two-sided with *α* = .05 and according to the intention-to-treat principle. Logistic regression analysis will be performed adjusted for centre and possible confounders. The economic evaluation will be performed from a societal perspective and all relevant costs will be measured, valued and analysed.

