## Recruitment {15}

Recruitment of participants started at 17 April 2019 and will be continued until the required number of participants will be enrolled. Infants with a unilateral inguinal hernia will be identified by the (fellow) paediatric surgeon at the outpatient clinic or neonatal intensive care unit (NICU) of the participating centres (Fig. 1). Currently (dd. August 24th 2021), 302 patients are included in this study. To enhance patient participation in this trial, one researcher coordinates the potential inclusions in all participating centres and strives to limit the number of eligible patients that were missed for inclusion. Over the past year, there has been some delay due to COVID-19; however, we expect to complete the recruitment of patients in 6 to 12 months.

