## Assignment of interventions: allocation

### Sequence generation {16a}

Study participants will be randomly assigned (1:1) to the intervention (contralateral exploration) or control group (no contralateral exploration) using Castor Electronic Data Capture (Castor EDC), a web-based electronic case record form and randomisation program that is compatible with the GCP guidelines [30].

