## Trial status

Recruitment of participants started at 17 April 2019 and will be continued until the required number of participants will be enrolled. The current protocol is v.1.8, date 30 June 2020. We expect to complete the inclusion of patients in March 2022.

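### The abstract gives 378, the number needed before loss to follow-up, as the number to be randomised; the sample-size section requires 416

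*Protocol article*

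**What the plan says.** Protocol article, Sample size {14}, sets out the calculation in three steps:

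- Control-arm rate: "The expected percentage of children requiring one or more reoperations because of MCIH in the first year following hernia repair is approximately 10" per cent.
- Effect: "We consider a reduction of children requiring reoperation from 10 to 2.5% as clinically relevant".
- Size before loss: "A total sample size of 378 patients is needed to detect such a reduction with a power of 0.80 at a two-sided alpha of 0.05".

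It then adds the attrition allowance: "Taking into account 10% loss to follow-up, we need to include 416 children". So 378 is the number needed before loss, and 416 is the number to enter.

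The abstract (Methods) says that infants will be randomised to one of the two strategies and attaches the smaller figure to that statement: "378 patients). Primary endpoint is the proportion of infants". It does not mention 416 or an allowance for loss.

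Recruitment {15} and Trial status both say that recruitment goes on until the required number is reached, and neither gives that number. Recruitment {15} reports progress ("Currently (dd. August 24th 2021), 302 patients are included in this study") and expects completion 6 to 12 months later. Trial status says "We expect to complete the inclusion of patients in March 2022". The section on discontinuing or modifying interventions {11b} says that withdrawn participants are not replaced.

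**The concern.** Both figures are presented as the number of infants who enter the trial, and they differ by 38. The reader of the abstract is told that 378 will be randomised. The reader of the sample-size section is told that 378 are needed after losses and that 416 must therefore be included. The sections that say when recruitment ends do not settle it.

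Withdrawn infants are not replaced, so the only provision for loss is the enrolment target itself. A trial that enrolled to the abstract's figure would have used no attrition allowance and would fall short of its planned power if the assumed 10% were lost.

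The allowance itself also needs a look: adding 10% to the evaluable number does not give the number from which a 10% loss leaves that evaluable number.

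**Working it through.** **Inputs** (Sample size {14}, except allocation): control rate p1 = 0.10; intervention rate p2 = 0.025; difference d = 0.075; two-sided alpha 0.05 (z = 1.960); power 0.80 (z = 0.842); loss 10%. Allocation is 1:1 (Sequence generation {16a}: "Study participants will be randomly assigned (1:1) to the intervention (contralateral exploration) or control group (no contralateral exploration"). The mean rate is p̄ = (0.10 + 0.025)/2 = 0.0625.

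**1. Reproducing 378.** The pooled-variance formula per arm is

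n = [1.960 × √(2p̄(1 − p̄)) + 0.842 × √(p1(1 − p1) + p2(1 − p2))]² / d²
= [1.960 × 0.3423 + 0.842 × 0.3382]² / 0.075² = 162.3.

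Rounded up, this is 163 per arm or 326 in total, which does not match. With the continuity correction,

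n′ = (n/4) × [1 + √(1 + 4/(n·d))]² = 188.06,

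rounded up to 189 per arm, or 378 in total. This matches the stated figure exactly, so I take the continuity-corrected formula as the planning basis.

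**2. The inflation.** 378 × 1.10 = 415.8, rounded to 416, which matches the stated target. To have 378 left after 10% loss, the number to enter is 378/0.90 = 420. In the other direction, 416 × 0.90 = 374.4 and 378 × 0.90 = 340.2.

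**3. Power at each evaluable number.** On the planning basis,

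power = Φ{[(d − 1/n) − 1.960 × √(2p̄(1 − p̄)/n)] / √[(p1(1 − p1) + p2(1 − p2))/n]}.

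For n = 170 per arm this is Φ[(0.06912 − 1.960 × 0.02626)/0.02594] = Φ(0.681) = 0.752. The uncorrected column omits the 1/n term.

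| Randomised | Evaluable after 10% loss | Per arm | Continuity-corrected | Uncorrected | Exact power, Fisher's test |
|---|---|---|---|---|---|
| 378 | 340 | 170 | 0.752 | 0.818 | 0.784 |
| 416 | 374 | 187 | 0.797 | 0.853 | 0.830 |
| 420 | 378 | 189 | 0.802 | 0.857 | 0.835 |

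**4. Do the dates identify the target?** From 17 April 2019 to 24 August 2021 is 860 days, so mean accrual is 302/860 × 30.44 = 10.7 per month. If that rate continued:

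- 378 would be reached after (378 − 302)/10.7 = 7.1 months, about 28 March 2022;
- 416 after (416 − 302)/10.7 = 10.7 months, about 14 July 2022;
- 420 after (420 − 302)/10.7 = 11.0 months, about 26 July 2022.

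All three fall within the 6 to 12 months given in Recruitment {15}. That window corresponds to 302 + 6 × 10.69 = 366 up to 302 + 12 × 10.69 = 430 infants. March 2022 fits 378 at the mean rate. Reaching 416 in that month would need about 15.8 to 18.4 infants per month, depending on the day in March.

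**The case against.** The strongest reply is that the trial has one derivation, and it is clear. The sample-size section separates the number needed for power from the number to include. The recruitment section follows it directly, so its required number most naturally means 416. On that reading the abstract merely left out the attrition allowance. This largely stands. It limits the consequence but does not remove the conflict, because the abstract ties 378 to randomisation.

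The power loss is also conditional. It needs both enrolment to stop at 378 and a full 10% loss, and it depends on the formula: at 170 per arm the results run from 0.75 to 0.82. The primary estimate is an adjusted odds ratio from logistic regression, not a continuity-corrected test, and missing data are to be multiply imputed, so lost infants are not simply discarded. These points stand as caveats. Imputation does not restore all the lost information, however, and the plan itself treats loss as a reason to enrol more infants.

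On 416 against 420, the gap is four infants, about 1%, and the 10% is itself a round assumption. That stands in full.

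Two stronger readings are tempting. One is that March 2022 shows the trial is really working to 378. The documents do not support this: it assumes that mean accrual continues, although the article reports a COVID-19 delay over the past year, and the article's other projection fits 378, 416 and 420 alike. The other is that the mismatch leaves the stopping point of an open-label trial to choice. That goes too far: the only derived enrolment target is 416, no interim analysis is planned, and the statistician and outcome assessors are described as blinded.

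**Conclusion.** The inconsistency is real and the correction is minor. The abstract gives the pre-loss number as the number to be randomised, the sample-size section requires 416, and the recruitment text names neither.

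If 378 were taken as the enrolment target and 10% were lost, power would fall from the planned 0.80 to about 0.75 on the planning basis. This rests on the planning rates of 10% and 2.5%, on a loss of exactly 10% shared equally between the arms, and on the continuity-corrected formula, inferred from its exact match to 378. By the uncorrected formula power would stay above 0.80.

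The inflation error is arithmetically clear but very small: 0.797 against 0.802 on the same basis. The calculation of 378 itself is sound, and neither the design nor the analysis is affected. The dates are not evidence for either target; they only need to agree with each other and with the target chosen.

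**What to change.** - In the abstract, describe 378 as the number of evaluable infants needed and give the enrolment target from the sample-size section as the number to be randomised.
- In Recruitment {15} and Trial status, name that target as a figure.
- In Sample size {14}, either keep 416 and state that a 10% loss leaves about 374 evaluable with power about 0.797 by the planning formula, or replace it with 420 (378/0.90).
- Give one expected completion date, consistent with the chosen target, in both Recruitment {15} and Trial status.

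The cost is a few lines of text. Keeping 416 needs no more infants than the sample-size section already requires; choosing 420 needs four more.
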